## Abstract

**Background:**

The present article presents the protocol for a randomised controlled trial to test the effectiveness of a group-based self-management support programme for recently diagnosed type 2 diabetes mellitus (T2DM) patients (one to three years post-diagnosis) and their partners. The course aims to support T2DM patients and their partners in successfully integrating diabetes care into their daily lives and hereby enhance self-management and diabetes-specific health-related quality of life. The content of the course is based on the Common-Sense Model of Self-Regulation (CSM). Furthermore, principles from the Social Cognitive Theory (SCT) and social support theories are integrated.

**Methods/Design:**

We aim to recruit 160 recently diagnosed T2DM patients and their partners from general practices in six different regions in the Netherlands. Patients need to be diagnosed with T2DM for one to three years and have to experience some degree of diabetes-related difficulties, as measured with a three-item screener. Participating patients and their partners are randomly allocated to the intervention or control condition. Participants in the intervention condition receive three monthly group sessions and a booster session three months later. Participants in the control condition receive a single information meeting. Data will be collected at baseline (T0), directly after the programme (T1) and six months post-programme (T2), including: self-management, diabetes-specific health-related quality of life, illness perceptions, attitudes, social support and empowerment. A three-level multilevel model will be used to compare change-scores between the conditions (intervention/control) on each outcome.

**Discussion:**

Our study will be the first to determine whether a group-based support programme based on the CSM is effective in enhancing self-management and diabetes-specific health-related quality of life in recently diagnosed T2DM patients. The important role of patients’ partners in effective diabetes care is also acknowledged in the study.

**Trial registration:**

Netherlands National Trial Register (NTR) NTR3302.

## Background

The prevalence of type 2 diabetes mellitus (T2DM) is increasing to epidemic proportions. Worldwide, more than 300 million people are diagnosed with T2DM and this number is expected to increase with 50% over the next 20 years [1]. Although T2DM usually starts as a mild condition, its chronic and progressive nature, the necessity for considerable lifelong lifestyle changes and serious long-term complications can place a major burden on individuals and their families [2,3], as well as health care systems [4].

Effective diabetes-management by patients has been proven to reduce the chances of serious adverse events [5] and, consequently, maintain quality of life [6,7] and keep health care costs manageable [8]. However, this does require patients to adopt a complex, multifaceted behavioural regimen, comprising the management of symptoms, treatment and lifestyle changes, as well as dealing with the psychological and psychosocial consequences related to the illness. Moreover, these behaviours need to be embedded within existing lifestyles, goals and priorities. Not surprisingly, a fair proportion of T2DM patients perceives the daily management of diabetes to be challenging or even burdensome and experiences difficulties in adequately engaging in self-care activities [9,10], which might consequently impact on quality of life [7].

Recognition of the comprehensiveness of diabetes management has led to the development of many self-management support programmes [11,12]. However, few have taken the specific challenges that may arise during the early phases of living with T2DM into account. Directly from the onset, T2DM patients are required to make lifestyle changes and adhere to treatment recommendations, mostly in the absence of diabetes-related symptoms or complaints. Hence, patients’ motivation to engage in self-management should therefore primarily result from their beliefs on the likelihood of adverse events occurring, as well as beliefs on personal control and effectiveness of treatment in order to prevent these serious undesirable events [13]. However, according to a review by Thoolen et al., [14], recently diagnosed patients tend to downplay the seriousness of their own condition. In addition, patients seem to be primarily concerned with the day-to-day hassles in diabetes management, rather than the possibility of serious complications in the long term. These attitudes and perceptions are likely to contribute to the finding that relatively few patients appear to be adequately engaged in the recommended (changes in) lifestyle behaviours within the first year after diagnosis [14].

In the past decades, patients’ perceptions on illness and treatment were identified to be important precursors for health behaviour change [15]. According to the Common-Sense Model of Self-Regulation (CSM) [16,17], illness perceptions act as a framework for the coping strategies chosen by patients to deal with the illness and are closely related to behavioural adaption, physical recovery and psychological well-being in various chronic illnesses [18]. Moreover, previous studies have shown that illness perceptions and, consequently, health related behaviours and outcomes can be successfully changed by short interventions based on CSM principles [19-21].

Accumulating evidence shows that not just the patients’ illness perceptions, but also the perceptions of partners are of great importance for understanding how patients respond to a chronic illness [22]. Illness perceptions held by partners guide their coping responses to the patients’ illness, including the way to give support to patients. Previous studies in T2DM have shown that social support can enhance as well as hinder self-management behaviours in patients, particularly dietary and exercise behaviours [22,23]. A small number of studies even suggested that partners’ illness perceptions can influence disease outcomes, with negative or incongruent perceptions being associated with worse physical, psychological and social functioning [24,25]. Hence, even though patients themselves are primarily responsible for managing their illness, it seems important that partners are structurally involved in diabetes care.

Given the importance to intervene at an early stage in T2DM and the promising results of previous studies based on the CSM, we developed the ‘Living with diabetes’ course: a group-based self-management support programme specifically tailored to T2DM patients and their partners in the first years of living with diabetes. With this new course, we aim to support both patients and partners in successfully integrating diabetes (care) into their daily lives and, hereby, enhancing self-management and diabetes-specific health-related quality of life in T2DM patients. Psychological and social aspects, including perceptions and attitudes, empowerment and social support, are integrated in the course because of their known important role in behaviour change [26] (Figure 1). A more detailed description of the content and underlying theories of the course can be found elsewhere ([name] et al., 2013 submitted).

**Figure 1 F1:**
[figure not shown]
Theoretical model of the programme.

### Aims and hypotheses

The primary aim of this study is to test the effectiveness of the ‘Living with diabetes’ course on enhancing self-management behaviours and diabetes-specific health-related quality of life in T2DM patients (one to three years post- diagnosis), compared to an attention control condition.

It is hypothesised that participation of T2DM patients in the group-based self-management support programme will result in:

a) Enhanced self-management and diabetes-specific health-related quality of life directly after the programme and at six months post-programme, as compared to an attention control condition.

Furthermore, we hypothesise that participation in the group-based self-management support programme will result in patients:

b) Holding more adaptive illness perceptions and attitudes towards T2DM;

c) Experiencing more activating partner support;

d) Feeling more empowered to manage their condition

Directly after the programme and at six months post-programme, as compared to an attention control condition.

## Methods/Design

### Study design

The effectiveness of the programme will be evaluated by a randomised controlled trial with two follow-up measurements: immediately after the programme (T1) and six months after T1 (T2) (Figure 2).

**Figure 2 F2:**
[figure not shown]
Flow of participants.

### Study population

Patients will be recruited via general practitioners (GPs) who are willing to invite eligible patients to participate in the study. In the Netherlands, all inhabitants are registered in a general practice. Therefore, a representative sample can be drawn.

#### Inclusion criteria

Being diagnosed with T2DM for one to three years, as recorded by their GP.

#### Exclusion criteria

● Not being able to speak, read and/or understand the Dutch language sufficiently according to their GP;

● Having insufficient mental or intellectual capabilities to participate in the study, according to their GP;

● Currently receiving treatment for severe psychological or psychiatric conditions, according to their GP;

● Recently diagnosed with a severe or life-threatening comorbid condition (e.g. cancer, CVA);

● Not experiencing any degree of diabetes-related difficulty or uncertainty, as assessed with a three-item screening questionnaire.

### Recruitment

The study population will be recruited from participating general practices in different regions in the Netherlands (North, West, Southwest and center). Eligible patients are selected from the medical records of the participating general practices and receive a written invitation for participation via their GP. Patients fill in an informed consent form as well as a short screening questionnaire, developed to identify patients who experience at least some degree of difficulty or challenge regarding their T2DM self-management. The questionnaire includes two questions of the Appraisal of Diabetes Scale (ADS) [27] and one statement of the Revised Illness Perception Questionnaire (IPQ-R) [28], assessing diabetes-related uncertainty, coping with diabetes and perceived consequences of diabetes on life. Patients with a total sum score of zero, indicating that they do not experience any difficulties or challenges regarding their diabetes management, are excluded from the study (see Table 1).

**Table 1 T1:** Screening questionnaire

1. How much uncertainty do you currently experience in your life as a result of being diabetic?				
None at all	Slight amount	Moderate amount	Large amount	Extremely large
(0)	(1)	(1)	(1)	amount (1)
2. How effective are you in coping with your diabetes?				
Not at all	Slightly effective	Moderately	Very effective	Extremely effective
(1)	(1)	effective (1)	(0)	(0)
3. My diabetes has major consequences on my life.				
Strongly disagree	Disagree	Neither agree nor	Agree	Strongly agree
(0)	(1)	disagree (1)	(1)	(1)

### Allocation to conditions

After obtaining the signed informed consent form, patients will be randomly allocated to the intervention or control condition. Randomisation will be conducted electronically by a researcher who is not involved in the study.

#### Intervention

Participants allocated to the intervention group are invited to take part in the group-based self-management support programme, together with their partner. Patients who do not have a partner, are instructed to bring a close friend or relative instead. Each course group consists of six to ten patients, accompanied by their partner (or close friend/relative). The course consists of three two-hour monthly meetings and one follow-up meeting (‘booster session’) after three months. The group sessions are led by two trained diabetes nurses or practice nurses and are delivered in medical and community centers in the different regions.

##### Framework

The ‘Living with diabetes’ course is based on the Common-sense Model of Self-Regulation [16,17], the Social Cognitive Theory [29,30] and principles of social support theories [31-33]. Content of the course is derived from previous psychosocial interventions focusing on illness perceptions [19,20,34]. The emphasis of the course is on stimulating beneficial illness perceptions and challenging misconceptions of T2DM in patients and partners. Another important aspect of the course is the enhancement of activating partner support for patients, by exploring patients’ needs for support and discussing supportive interactions with patients and partners. Goal setting and action plan development are used as techniques to improve patients’ empowerment and elicit self-management behaviour change. All sessions are group-based, providing the opportunity for peer modeling, social reinforcement, motivation and emotional support.

##### Materials

Participants receive a handbook with (homework) assignments, and practical and theoretical information about the topics discussed during the sessions. In addition, basic information about diabetes and its treatment is provided in the handbook. For the diabetes or practice nurses who guide the course sessions, a detailed manual has been developed.

##### Pilot

The course was pilot-tested on feasibility and acceptability in November and December 2011. Sixteen T2DM patients and eight partners from a general practice in the region of Utrecht participated in the pilot-study (attrition rate 21.6%). During the pilot, all course sessions were led by a health psychologist in order to evaluate whether the correct psychological models and techniques were used. During the first session, a practice nurse was also present to provide medical information on T2DM. Feasibility and acceptability of the course were explored by means of an evaluation form at the end of the course and by feedback of the participants during the course sessions. Based on the evaluation of the pilot, the manual was adapted and a screening questionnaire was developed for the RCT to ensure that only T2DM patients who experience some degree of difficulties or uncertainties will participate.

#### Attention control condition

Participants in the attention control condition are invited to a single 1.5 – hour information meeting, together with their partner (or close friend/relative). During this meeting, patients and their partners receive medical information about diabetes (e.g. causes, complications, treatment) from a professor in general practice and diabetes care. The information meeting serves as an attention control condition to control for the attention paid to being diagnosed with T2DM when participating in this study. Hence, the information that patients and partners receive during the information meeting is provided according to the classical didactic method; i.e. providing information that is important from a medical point of view, but not tailored to the specific and more comprehensive needs of the patients.

### Measures

Patients fill in a questionnaire at baseline (T0), immediately after the programme (T1) and six months post-programme (T2) to assess the effectiveness of the programme on the longer term. The primary outcome measures are self-management and diabetes-specific health-related quality of life. Secondary outcomes are illness perceptions, attitudes towards diabetes, partner support and empowerment.

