#### Primary outcome measures

Self-management is measured by using the revised Summary of Diabetes Self-Care Activities measure (SDSCA) [35]. The revised SDSCA contains 11 items, measuring six separate domains: general diet (2 items), specific diet (2 items), exercise behaviours (2 items), glucose monitoring (2 items), foot care (2 items) and smoking (1 item). Ten items are rated on an eight -point Likert scale, measuring the number of days a certain self-care behaviour is performed during the last week (0–7 days). The 11^th^ item measures smoking (yes/no) and the number of cigarettes smoked. Each of the domains is measured separately. The revised SDSCA shows an adequate internal consistency and test-retest reliability and is sensitive to change. The measure has been validated against other measures of diet and exercise [35].

Diabetes-specific health-related quality of life is assessed by the Problem Areas in Diabetes scale (PAID) [36], measuring diabetes-related emotional distress. The PAID consists of 20 items on a five -point Likert scale, ranging from 0 (not a problem) to 4 (a serious problem). Scores are transformed into a 0–100 scale for interpretation, with higher scores indicating greater diabetes-related emotional distress. The PAID has a strong concurrent and discriminant validity [37], has been proven to be responsive to change [38] and has been validated for Dutch T2DM patients [36,37].

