### Sample size

The sample size calculation is based on detecting a clinically relevant change on the PAID, as a result of the programme. Since there is no consensus on the minimal important difference (MID) on the PAID, we decided to set the MID at half a standard deviation (SD); a commonly used solution when scores have no direct interpretation and no clinical results exist to determine a relevant percentage [42]. In Dutch T2DM patients, the SD found on the PAID was 20, with a mean score of 22.5 points (scale 0–100) [36]. To establish a 10-point difference with the power set at 80% and the α at .05 (two-sided), 63 patients are needed in each condition (intervention/control). However, taking the clustering of patients within groups into account, an oversampling of 15% is needed to conduct multi-level analyses. When accounting for an additional drop-out of 10%, 2 × 80 patients will have to be recruited.

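### The primary set is seven separately measured endpoints at two unranked follow-ups, but α .05 and 80% power are set for one PAID comparison; no reading that uses the full set keeps both figures

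*Protocol article*

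**What the plan says.** - **Measures** (Protocol article): "The primary outcome measures are self-management and diabetes-specific health-related quality of life". Neither construct is placed ahead of the other.
- **Primary outcome measures**: "The revised SDSCA contains 11 items, measuring six separate domains", and "Each of the domains is measured separately". No total score is named. The six domains are general diet, specific diet, exercise, glucose monitoring, foot care and smoking. The smoking item records yes/no and a cigarette count; the other ten items count days per week. Quality of life is a single PAID score from 0 to 100.
- **Aims and hypotheses**, hypothesis (a): "Enhanced self-management and diabetes-specific health-related quality of life directly after the programme and at six months post-programme". The two follow-ups are joined by a plain 'and', and neither is ranked.
- **Abstract, Methods/Design**: "A three-level multilevel model will be used to compare change-scores between the conditions (intervention/control) on each outcome".
- **Statistical analysis**: a three-level model over T0, T1 and T2, with a condition effect and a condition × time interaction. The section does not say which term decides, and it describes the outcomes as continuous.
- **Sample size**: "The sample size calculation is based on detecting a clinically relevant change on the PAID". The inputs are a 10-point difference, SD 20, two-sided α .05 and 80% power, giving 63 per arm. After 15% for clustering and 10% for drop-out this becomes 2 × 80.

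**The concern.** The set of endpoints called primary and the comparison that the trial is sized for are different things. The Discussion makes wider use of the course depend on its being proven effective, yet the article does not identify the result that would prove it. With seven endpoints and two follow-ups of equal standing, that choice could be made after the results are seen. An α adjustment added later would also use up power that the sample size does not provide for. A smaller point sits within this: the yes/no part of one primary domain, smoking, does not fit the description of the outcomes as continuous.

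**Working it through.** **Inputs from the article.** PAID difference 10, SD 20, α .05 two-sided, power 80%, inflation 15% and 10%; 1 PAID score + 6 SDSCA domains = 7 endpoints; 2 follow-ups. The article gives no correlations, so those below are assumptions and a range is shown.

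**1. The stated sample size reproduces.** n per arm = 2(1.960 + 0.842)² × 20²/10² = 62.8, so 63. Then 63 × 1.15 = 72.45. Adding 10% gives 79.7, and dividing by 0.9 gives 80.5. Both agree with 80. The calculation is for one PAID comparison.

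**2. If any one significant result counts.** With k independent tests and no true effect:
- either direction: 1 − 0.95^k
- in favour of the course: 1 − 0.975^k

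Seven tests means one per outcome; 14 means each outcome tested at T1 and at T2. Correlated cases come from multivariate-normal simulation.

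| Assumption | 7 tests, either direction | 7 tests, favouring course | 14 tests, either direction | 14 tests, favouring course |
|---|---|---|---|---|
| Independent | 30% | 16% | 51% | 30% |
| 0.3 between outcomes, 0.6 between times | 27% | 14% | 43% | 22% |
| 0.7 between outcomes, 0.9 between times | 18% | 9% | 24% | 12% |

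A single two-sided .05 test gives 5% in either direction and 2.5% in favour of the course.

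**3. If all must succeed.** The chance of a false claim is then at most 5%, but power falls. Assume 80% power for PAID at each follow-up. The chance that both are significant is the bivariate-normal probability that both variables lie below 0.842. This is 0.80² = 64% if independent, about 70% at correlation 0.6 and about 75% at 0.9. Requiring the SDSCA domains as well can only lower it. By how much cannot be derived, because the article gives no SDSCA effect size or SD.

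**4. If α is split afterwards.** With 63 per arm, the standardised PAID effect is 10/(20√(2/63)) = 2.806.
- Bonferroni over 7: critical value 2.690, power Φ(2.806 − 2.690) = 55%.
- Bonferroni over 14: critical value 2.914, power Φ(2.806 − 2.914) = 46%.

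Restoring 80% power would need about 100 per arm (7 tests) or 113 per arm (14 tests) before inflation.

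**The case against.** **An analysis plan may hold the multiplicity rule.** This stands as far as it goes: the absence of a multiplicity method from a journal article is no finding in itself. But the primary set and the sample size are both fixed in this article and do not match. Step 4 shows that a later α split would not restore the match at 63 per arm.

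**A reader might infer a 30–50% chance of wrongly declaring the course effective.** The article does not support that. Those figures count significance in either direction, whereas a false finding of benefit must favour the course, which roughly halves them. They also need a rule that one significant result is enough. The article never states such a rule, and the 'and' in hypothesis (a) can be read the other way. The 51% end further requires T1 and T2 scores of the same patients to be independent, which is implausible.

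**A reader might also infer that both α and power fail under every reading.** They do not. An all-must-succeed rule keeps α at or below 5%, and an any-one rule leaves the planned PAID power intact. Each reading loses one of the two.

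**The number of tests is partly inferred.** The article names two constructs. Seven endpoints follow from the separate domains and the lack of a total score. Fourteen tests is one reading of the model; a joint condition × time test would give one test per outcome. Hence the range from 7 to 14.

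**Conclusion.** The mismatch is real and visible in the article itself: two unranked primary constructs, seven endpoints as measured, two unranked follow-ups, and one α and power statement that covers a single PAID comparison. No reading that uses the full primary set keeps both α .05 and 80% power.

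The size depends on a decision rule that is not stated. Under an any-one rule, the false-positive chance in favour of the course is about 16% to 30% if the tests are independent, 14% to 22% at the moderate assumed correlations and 9% to 12% at the high ones. Even the lowest is more than three times 2.5%. Under an all-must-succeed rule the loss is in power: about 70% for PAID at both times, given 80% per test and an assumed correlation of 0.6. The structural point rests on the text alone; the percentages rest on the assumptions named with them.

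**What to change.** 1. Name the PAID condition contrast at one follow-up as the single confirmatory test at two-sided .05. T2 would suit, because the Measures section ties that assessment to longer-term effectiveness. This matches the existing calculation of 63 per arm, 80 after inflation.
2. Only if that test is significant, test PAID at the other follow-up and the five day-count SDSCA domains at the same named follow-up, with a Holm correction over these six tests.
3. Report the smoking yes/no item descriptively or with a logistic multilevel model.

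**Cost.** The change is to wording only, and no patients are added. Self-management, which the primary aim names first, moves behind PAID, and its single domains face a stricter threshold (.05/6 = .0083 at the first Holm step).

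**Alternative.** If the sponsor wants self-management to stay co-primary, apply Holm across the primary endpoints at one named follow-up and restate the PAID power. At the strictest step over seven tests it is about 55% with 63 per arm.
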